##### 3.6.1.2. Blood Pressure Measurement Plan According to Office Blood Pressure Levels

Repeated examination and/or measuring BP levels at home will be performed as follows:

Participants with normal BP (<130/ <85), will be re-examined on at least one further office visit (1–2 week intervals).Participants with suspected high-normal BP (130–139 and 85–89), will have repeated office visits (2 at 1–4 week intervals) required and will be asked to monitor blood pressure for at least 5 (preferably 8) consecutive days at home (HBPM).Participants with suspected hypertension (≥140 and ≥90), repeated office visits (3 or 4 visits at 1–4 week intervals) for re-examination will be required. Also, they will be asked to monitor blood pressure for 8 consecutive days at home (HBPM). Those diagnosed with HBP during this period (see HBPM below) will be referred to the ambulatory blood pressure monitoring (ABPM) service at the INC-ICh.The diagnosis will be made on a single visit, if BP is ≥180/≥110 mm Hg on the first set of three measurements. Then the participant will be immediately scheduled for a clinic visit at the INC-ICh to receive appropriate treatment. The day of the diagnosis of hypertension will be considered the date of disease onset.

Participants who are diagnosed with HBP at another facility at any time during the study will be requested to immediately notify principal investigators. These participants will be asked to schedule a visit at the INC-ICh prior to starting any medical treatment, to confirm the diagnosis and to complete the “end of the study” visit. Also, participants who are diagnosed with HBP and initiate and maintain regular antihypertensive therapy (more than 2 weeks) will be eliminated, according to the criteria of the umbrella cohort (35). The date of disease onset will be considered as the date of confirmation of the diagnosis and/or the date of initiating antihypertensive therapy.

For those diagnosed with HBP during one of the follow-up visits at INC-ICh, the date of disease onset will be recorded as the date of the visit. Additionally, all participants will be contacted by telephone or by email every 6 months to verify whether they have been diagnosed with HBP and/or if they are taking antihypertensive therapy (see Figure 1).

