### 3.5. Variables (Identification, Definition, and Measurement Scales)

#### 3.5.1. Definition of Variables

Dependent-variable of interest: Incidence of hypertension.Independent-variables of interest: Periodontal-related parameters and oral-related microbial profiles.Oral health covariates: Oral health related quality of life; diet changes; perception of need for dental treatment; xerostomia; use and functionality of removable dental prostheses; oral hygiene (presence of biofilm and dental calculus); number of natural teeth present; dental caries; root debris and gingival bleeding.

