### 3.6. Dependent Variable

#### 3.6.1. Systemic Arterial Hypertension

Blood pressure assessment will be performed every 2 years in accordance with the *2020 International Society of Hypertension Global Hypertension Practice Guidelines* (39). Hypertension will be diagnosed when (1) a person's systolic blood pressure (SBP) in the office is ≥140 mm Hg and/or their diastolic blood pressure (DBP) is ≥90 mm Hg after at least 3 repeated examinations and (2) when a person's systolic blood pressure (SBP) at home (HBPM) is ≥135 mm Hg and/or their diastolic blood pressure (DBP) is ≥85 mm Hg. Classification values are charted below (39).

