##### 3.6.1.1. Office Blood Pressure Measurement Classification (SBP/DBP, mm Hg)

Normal BP, <130 and <85High-normal BP, 130–139 and/or 85–89Grade 1 hypertension, 140–159 and/or 90–99Grade 2 hypertension, ≥160 and/or ≥100

*3.6.1.1.1. Preparation and Position*. Before office BP measurements, participants will be advised to have an empty bladder, not to exercise and not to smoke, drink coffee or tea, for at least 30 min on the visit day. Participants will be seated in a quiet room (neither participant nor staff should talk before, during and between measurements) with comfortable temperature for at least 5 min before the first evaluation, arm resting on table with mid-arm at heart level; back supported on a chair; legs uncrossed and feet flat on the floor (39).

*3.6.1.1.2. Monitoring Schedule*. BP will be measured in the right arm three times with 1 min between them with a validated electronic (oscillometric) upper-arm cuff device (40–42) according to the individual's arm circumference. The average of the last 2 measurements will be calculated. If one of the three measurements is remarkably different, a fourth measurement will be taken. If BP of first reading (first three measurements) is less than 130/85 mm Hg no further measurement is required (39).

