##### 3.6.1.3. Home Blood Pressure Monitoring

In order to reduce the number of possible false readings (high possibility of white coat or masked hypertension), high-normal BP and hypertension cases will be instructed, trained and asked to monitor blood pressure at home. The participants will be guided on how to select an appropriate HBPM device, how to measure their own BP (preparation, position and monitoring schedule) and will be provided some practical recommendations for optimal HBPM performance (43–45).

*3.6.1.3.1. Preparation and Position*. The participant should avoid smoking, caffeine and exercise for 30 min before measurements. They should have an empty bladder, and rest quietly in a comfortable seated position with the back supported, legs uncrossed, and both feet on the floor for 5 min before taking home BP measurements. The cuff of the device should be placed directly above the elbow and pulled taut, with the arm supported on a flat surface. Avoidance of talking or using electronic devices during BP measurements will be required. The participant will be instructed not to share the device with anyone unless this is equipped to store readings for multiple people and carry out a periodic check-up of the device.

*3.6.1.3.2. Monitoring Schedule*. HBPM will be based on 2 measurements taken at least 1 min apart in the morning and evening. Morning measurements should be made before breakfast and evening measurements should be taken before going to bed.

Current guidelines recommend that the average of all these values should be used with the exception of the first day, which should be discarded for clinical decision-making. If there is a discrepancy between office BP and home BP readings, a home BP-based diagnosis should take precedence (46). HBPM reference values are as follows:

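### Sections 3.6.1 to 3.6.1.4 give conflicting rules for incident hypertension, so the same readings can be a case under one section and a non-case, or outside the repeat-visit plan, under another

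*Protocol article*

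**What the plan says.** Section 3.5.1 names the outcome: "Dependent-variable of interest: Incidence of hypertension". Five places in Section 3.6.1 and its subsections then bear on who has it.

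- **Definition (3.6.1).** The office part is met when systolic pressure "in the office is ≥140 mm Hg and/or their diastolic blood pressure (DBP) is ≥90 mm Hg". It is joined to a home part (systolic at least 135 and/or diastolic at least 85) by the words "≥90 mm Hg after at least 3 repeated examinations and (2) when a".
- **Office classification (3.6.1.1).** High-normal, grade 1 and grade 2 are each written with *and/or*. For a first reading that "is less than 130/85 mm Hg no further measurement is required".
- **Measurement plan (3.6.1.2).** The suspected-hypertension row reads "Participants with suspected hypertension (≥140 and ≥90), repeated office visits (3 or 4 visits at 1–4 week intervals) for re-examination will be required". The high-normal row likewise joins 130–139 and 85–89 with *and*. Participants in the normal row "will be re-examined on at least one further office visit". A diagnosis can be made at one visit at 180/110 or above, with no home reading.
- **Home monitoring (3.6.1.3).** High-normal and hypertension cases are asked to monitor at home. If office and home readings disagree, "a home BP-based diagnosis should take precedence".
- **Home threshold (3.6.1.4).** A home reading of at least 135 and/or at least 85 is labelled hypertension.

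**The concern.** These sections should together produce one yes-or-no outcome for each participant. They differ in two ways that matter. The operator joining systolic and diastolic pressure changes between the definition and the plan that collects the confirming visits. The relation between office and home results changes between the definition and the home-monitoring section.

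The classification feeds the first and third hypotheses in Section 2.3, the 21.5% incidence in the sample size of Section 3.3.1, and the split by hypertension status in the microbiome sampling of Section 3.3.2. A later derivation rule can choose between two codings of recorded data. It cannot recover repeat visits that were never ordered.

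**Working it through.** The plan states no figure on this point, so there is none to reproduce. The check applies each rule as written to example readings. The readings are illustrative and do not come from the documents.

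**Step 1: systolic and diastolic operator**

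| Office reading | Office cut-off in 3.6.1 | Class in 3.6.1.1 | Row in 3.6.1.2 |
|---|---|---|---|
| 150/95 | met | grade 1 | suspected hypertension |
| 145/80 | met | grade 1 | none |
| 125/95 | met | grade 1 | none |
| 135/87 | not met | high-normal | high-normal |
| 135/80 | not met | high-normal | none |

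The classification in 3.6.1.1 gives every one of these readings a class. The plan in 3.6.1.2 leaves out each reading in which only one component is raised: it is not normal, because normal needs both components low, and it is in neither higher row, because each of those needs both components raised. For 145/80 and 125/95 the office cut-off is met, but no passage orders the three or more repeat examinations on which 3.6.1 makes the diagnosis depend. Home monitoring is a separate matter: 3.6.1.3 asks for it in high-normal and hypertension cases, and by the classes of 3.6.1.1 that includes these participants.

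**Step 2: office and home relation**

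Each participant with both results falls in one of four cells. The definition in 3.6.1 can be read as requiring both parts (its plain wording) or as listing two alternative routes. Section 3.6.1.3 lets the home result decide any disagreement, so under it case status equals the home result.

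| Office part | Home part | 3.6.1, both required | 3.6.1, either route | 3.6.1.3, home decides |
|---|---|---|---|---|
| met | met | case | case | case |
| met | not met | non-case | case | non-case |
| not met | met | non-case | case | case |
| not met | not met | non-case | non-case | non-case |

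- Both required against home decides: they differ in the third row. Office 135/87 with home 140/88 is an example, and it can arise because the plan sends high-normal participants to home monitoring.
- Either route against home decides: they differ in the second row, the white-coat pattern. Office 150/95 with home 125/80 is an example.

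Neither reading of 3.6.1 agrees with 3.6.1.3 in all four cells. Rereading the definition moves the conflict from one group to another.

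**Step 3: smaller departures**

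The single-visit diagnosis in 3.6.1.2 meets neither the repeat-examination nor the home requirement of 3.6.1. Below 130/85, one section asks for nothing further and the next asks for at least one more visit.

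**The case against.** The strongest reply is that 3.6.1.2 is a measurement plan, not an outcome definition. Its *and* may be loose shorthand for 140/90, coming directly after the classes have been set out with *and/or*. That may well be the intention. But the same cut-offs carry a different operator in the preceding subsection, and nothing tells staff which to follow when deciding who returns for repeat visits.

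A second reply is that 3.6.1.3 already supplies a tie-break, perhaps meant for clinical decisions and not for the research endpoint. If it does govern the endpoint, the joint requirement in 3.6.1 is wrong as written. If it does not, the text fails to say so, and 3.6.1.4 labels the home threshold hypertension outright. The single-visit route may be a deliberate exception, and the statement about no further measurement may concern only that day's readings. Both are easily settled in the wording.

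Four stronger inferences are tempting and are not supported:

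- *Isolated elevation never reaches home monitoring.* Section 3.6.1.3 asks hypertension and high-normal cases to monitor at home, so what is not ordered is the repeat office visits.
- *Masked hypertension in general is coded inconsistently.* Participants with normal office pressure get no home reading under any section. The conflict concerns those with high-normal office pressure.
- *Most raised readings are lost.* Any such share would need a mean, a spread and a correlation of pressures, and the documents give none.
- *The error differs by periodontitis status through access to home devices.* The documents say nothing about who has access. How to code a participant without a home record is a detail that an analysis plan commonly settles.

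**Conclusion.** The contradiction stands in the current text and concerns the dependent variable. Followed literally, the sections do two things. They leave participants with isolated systolic or isolated diastolic elevation outside the rows that order the repeat office examinations required by the definition. They also code a participant with high-normal office pressure and raised home pressure as a non-case under 3.6.1 and a case under 3.6.1.3 and 3.6.1.4.

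The first result rests on reading *and* in 3.6.1.2 as written. The second rests on reading 3.6.1 as requiring both parts; the other reading shifts the conflict to white-coat readings. The effect on incidence, on power and on the estimated association cannot be sized from the documents, and no direction of bias is claimed. The inconsistency for normal office pressure is minor: it has not been shown to change who is a case.

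**What to change.** Reconcile Sections 3.6.1 to 3.6.1.4 into one research-endpoint algorithm that meets these conditions:

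1. Every office reading falls in exactly one work-up row, and the definition, the classification and the work-up rows are consistent with each other.
2. One relation between office and home results is stated and applied to all participants. The single-visit route is either named as an exception in the definition or brought into line with it.
3. The outcome under the alternative office–home reading is derived as a sensitivity analysis, which needs office and home results to be stored separately.
4. The two statements on further measurement at normal office pressure are made consistent.

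Which clinical rule to adopt at each step is for the investigators. The cost is protocol wording and one derivation rule. Depending on how the work-up rows are settled, a material number of additional participants may enter the confirmatory visits that the plan already runs, so the visit load should be checked before the text is fixed.

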## 3. Methods

### 3.1. Ethical Aspects

In accordance with the Regulation of the General Law of Health in Matters of Health Research, in the Second Title (Of the Ethical Aspects of Research in Human Beings) article 17, this research is classified among the Investigations with Minimum Risk, since no adverse effects have been reported from periodontal measurement on teeth (34). Written informed consent will be required. The confidentiality of the information will be ensured and each of the participants will be given a health diagnosis.

We must highlight that all participants will be given detailed information and recommendations about their individual health (blood pressure levels, lab tests and periodontal evaluation) immediately after every evaluation and referred to specialized treatment whenever needed. However, we should highlight that receiving medical and/or periodontal treatment will depend only on each participants' decision.

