#### 3.4.3. Elimination Criteria

People who develop hypertension and initiate and/or maintain regular and active antihypertensive therapy.People who develop systemic and uncontrolled diseases that may interfere with the severity of periodontitis.People who initiate and maintain regular and active periodontal treatment during the study follow-up.People who develop some forms of periodontitis that require regular antibiotics.People who undergo dental procedures that involve implant placement.

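### Participants diagnosed with hypertension elsewhere are asked to visit INC-ICh before any treatment, with no exception for severe hypertension, so the request followed as written can postpone urgent treatment

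*Protocol article*

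**What the plan says.** Section 3.6.1.2 of the protocol article describes two routes to a hypertension diagnosis.

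- **Found by the study.** A single visit is enough "if BP is ≥180/≥110 mm Hg on the first set of three measurements", and the participant is then "immediately scheduled for a clinic visit at the INC-ICh to receive appropriate treatment". Below that level, suspected hypertension needs 3 or 4 office visits 1 to 4 weeks apart and 8 days of home monitoring.
- **Found elsewhere.** Such participants "will be requested to immediately notify principal investigators". The next step is: "These participants will be asked to schedule a visit at the INC-ICh prior to starting any medical treatment, to confirm the diagnosis". The same visit also closes out the participant's follow-up.

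Three other statements bear on the point.

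- Section 3.6.1.2 says that diagnosed participants who "initiate and maintain regular antihypertensive therapy (more than 2 weeks) will be eliminated", and dates onset as "the date of confirmation of the diagnosis and/or the date of initiating antihypertensive therapy".
- Section 3.4.3 lists among those eliminated "People who develop hypertension and initiate and/or maintain regular and active antihypertensive therapy", with no mention of 2 weeks.
- Section 3.1 says that "receiving medical and/or periodontal treatment will depend only on each participants' decision".

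**The concern.** The request for outside diagnoses is unqualified. It applies to all treatment and does not separate a mildly raised pressure from a severe one. The protocol draws exactly that distinction for its own readings: at 180/110 mm Hg or above it drops repeat confirmation and moves directly to treatment.

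The outside route is one the plan expects to be used. Study blood pressure assessments are 2 years apart (section 3.6.1), and participants are contacted every 6 months partly to learn whether they have been diagnosed in between (section 3.6.1.2).

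What is at stake is participant safety. Someone with a severe outside reading who complies goes untreated until the INC-ICh visit, for the sake of a confirmation that the protocol itself would not require beyond one visit at that level.

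**Working it through.** The plan gives no figure to reproduce, and no sample size or power formula bears on the point. The check is a comparison of the statements.

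**1. Same pressure, two routes.**

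| | Measured by the study at ≥180/≥110 mm Hg | Measured elsewhere at ≥180/≥110 mm Hg |
|---|---|---|
| Confirmation | One visit suffices | INC-ICh visit requested to confirm |
| Treatment | Immediate scheduling for it | Requested to follow the visit |
| Word on timing | Scheduling is immediate | Notification is immediate |
| Day limit | None | None |
| Severity exception | Is itself the exception | None |

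Neither route gives a number of days, so a missing day limit does not separate them. What separates them is the order of treatment and visit, and the absence of a severity exception in the outside route.

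**2. Is an exception stated somewhere else?** Sections 3.1, 3.4.3, 3.6.1 to 3.6.1.4 and 5 contain no severity exception or urgent-care clause for outside diagnoses. The referral in section 3.1 follows the study's own evaluations and does not set the request aside.

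**3. Does the outcome need an untreated visit in severe cases?** No. Under section 3.6.1.2 onset may be dated from the start of therapy, so a participant who is treated first already has a usable onset date.

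**4. Would a participant who is treated first stay in the study?** The two elimination statements differ. Section 3.6.1.2 eliminates after more than 2 weeks of regular therapy. Section 3.4.3 names starting and/or maintaining regular therapy and gives no such tolerance. The tolerance therefore rests on section 3.6.1.2 alone, and an exemption for severe cases has to say how those participants are handled.

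**5. What would the exemption cost in samples?** Saliva and plaque at the end of follow-up are taken only from participants selected for the microbiome study (section 5.1). That is 200 of the projected 1,212 (sections 3.3.1 and 3.3.2): 200 / 1,212 = 0.165, about 17% of the cohort. The share among people who develop hypertension may differ, because section 3.3.2 plans sampling by hypertension status. Only the severe or urgent cases within that group would give samples on treatment.

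**The case against.** The strongest reply is that nothing here withholds treatment. Participants are asked, not instructed. Section 3.1 leaves treatment to them, the outside physician receives no instruction, and the onset rule already provides for people who treat first. The visit is at a national cardiology institute, so the request also leads to specialist care. All of this stands. It lowers the chance of harm, but it does not change what a participant who complies is asked to do.

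A second reply is that a journal article leaves visit windows and urgent-care detail to the full protocol or to the umbrella cohort's procedures. That stands for the missing day limit, which is not pressed here. It does not answer the request itself, which the article states in full and without qualification.

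A third reply is that confirming before treatment has good reasons. It guards against white-coat diagnoses (section 3.6.1.3), protects the outcome definition and gives close-out samples free of drug effects. That stands for ordinary cases. It is weak at 180/110 mm Hg or above, where the protocol accepts a single visit.

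Finally, the wording could mean only that the visit be booked before treatment starts. But the visit is meant to confirm the diagnosis and close out follow-up, which points to an untreated visit. If booking alone was meant, a safety instruction is ambiguous and the same sentence cures it.

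**Conclusion.** The point holds as a gap in participant-safety wording. The request for outside diagnoses has no exception for severe hypertension, is out of step with the protocol's own rule at 180/110 mm Hg, and can postpone urgent treatment if followed as written. It should be corrected because the change is small and the foreseeable harm is not trivial.

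Its size cannot be given. The document offers no basis for estimating how many participants aged 20 to 50 at entry, and free of hypertension then, would have a severe reading first found elsewhere, or how long they would wait. There is no effect on sample size or power.

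Three stronger readings are tempting but unsupported:

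- **That the protocol bars or withholds treatment.** It makes a request and leaves the decision to the participant.
- **That confirmation would delay treatment by weeks.** The schedule for suspected hypertension would span 2 × 1 = 2 weeks (3 visits, 1 week apart) to 3 × 4 = 12 weeks (4 visits, 4 weeks apart). The article does not say that it applies to outside diagnoses, and a reading of 180/110 mm Hg or above at INC-ICh would be settled in one visit.
- **That a participant treated early is safe from elimination for 2 weeks.** Section 3.4.3 states no such tolerance.

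The conclusion assumes that some participants will act on the request and that it asks for an untreated visit.

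**What to change.** Add to section 3.6.1.2, after the request:

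- Treatment must not wait for the INC-ICh visit when the outside blood pressure is ≥180/≥110 mm Hg or the treating physician judges that it should start.
- These participants should be seen promptly at INC-ICh.
- Their treatment status is recorded at the end-of-study visit.
- Their onset is dated from the start of therapy, as the section already allows.
- They still complete the end-of-study visit and count as incident cases, whatever section 3.4.3 says about starting therapy.

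Keep confirmation before treatment for everyone else.

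The cost is a few sentences and one recorded item. The downside is that a few diagnoses will be confirmed, and a few close-out measurements and samples taken, on treatment. The recorded treatment status lets the analysis identify them.
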